## **6.1 Data and Safety Monitoring Board (DSMB)**

The Data and Safety Monitoring Board (DSMB) will review safety reports after 50% of the trial population has completed follow-up and can, at their discretion, request additional safety analyses. The DSMB will make recommendations as it sees fit regarding the conduct and continuation/stopping of the trial to ensure the safety of the participants and the integrity of the trial.

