| Duration of Treatment | Treatment will be delivered for 48 hours post-catheter insertion.                                                                                                                                                                                                                                                                                                                                                                                                                                                                                                                                                                                                                                                                                                                                                                                                                                                                                                                                                                                                                                                                                                                                                                                                                                                                                                                                                                                                                                                                                                                                                                                                                                                                                                                                                                                                   |

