### **3. Study Design**

#### **3.1 Study Overview**

EPOCH CardioLink-10 is a randomized, double-blinded, parallel-group, multicentre study of superficial parasternal intercostal plane blocks with 0.2% ropivacaine versus sham block with 0.9% normal saline administered via catheters placed under ultrasound guidance in patients undergoing cardiac surgery through a median sternotomy. Patients meeting inclusion criteria who provide informed consent will be randomized in a 1:1 fashion into the intervention or control group. Based on the below sample size calculation, approximately 340 patients will need to be randomized to detect important differences. This will be a multicentre trial (up to 4 sites in Canada), with usual institutional anesthetic and postoperative analgesia management being provided to all enrolled patients. Patients will be followed prospectively during the hospitalization with regular assessments of postoperative pain and recovery, as well as during follow-up visits at 6 weeks and 3-6 months following their operation. To reduce lost-to-follow-up, patients will be asked to provide up to two telephone contact numbers.

The four Canadian trial sites are:

- 1) St. Michael's Hospital, Toronto, ON (Recruiting)  
PI: [name]
- 2) QEII Health Sciences Centre, Halifax, NS (Recruiting)  
PIs: [name], [name] [name]
- 3) Foothills Medical Centre, Calgary, AB (Recruiting)  
PI: [name]; Co-I: [name]
- 4) Royal Columbian Hospital, New Westminster, BC (Recruiting)  
PI: [name]; Co-I: [name], MN

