## 5. Study Procedure and Visits

### 5.1 Summary of Visits

Patients will be screened at an initial preoperative visit at which point eligibility will be determined. Patient outcomes will be assessed throughout their postoperative hospital stay as detailed above. Two follow-up telephone visits after the operation will be scheduled. The first will be at 6 weeks  $\pm$  2 weeks post surgery and the second will be at 3 months  $\pm$  4 weeks.

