- Attempts to obtain the 3-month data can continue for up to 6 months post-surgery before it will be considered a protocol deviation or the participant deemed lost-to-follow-up

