In the present investigation, each study visit will include safety monitoring. Adverse effects that will be specifically collected include infection, hematoma/hemorrhage, vascular injury, pneumothorax/hemothorax, allergic reaction/anaphylaxis, postoperative nausea/vomiting, pruritus and LAST. Adverse event data will be reported in the study publication.

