### 3.2.2 *Safety Population*

The Safety Population will include all participants in whom a block catheter was placed, and a dose of study treatment was administered. Treatment classification will be based on the actual study treatment received. The Safety Population will be the primary population used for safety analyses.

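### The only scheduled DSMB safety review waits for an undefined completion of follow-up, and the Safety Population leaves out insertion injuries in patients who were never dosed

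*Combined protocol and SAP*

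**What the plan says.** **Review timing.** Protocol 6.1 says that the DSMB "will review safety reports after 50% of the trial population has completed follow-up" and that it "can, at their discretion, request additional safety analyses". No other review is scheduled, and SAP 4.1 plans no interim analysis. Section 6.1 does not say when follow-up is complete. Three other places bear on it:

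- Protocol 5.1 sets two telephone visits; "the second will be at 3 months", ± 4 weeks.
- Protocol 5.2, under the second telephone visit: "Attempts to obtain the 3-month data can continue for up to 6 months post-surgery".
- Protocol 3.1 describes patients as followed in hospital, "as well as during follow-up visits at 6 weeks and 3-6 months following their operation".

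On exposure, the Synopsis states: "Treatment will be delivered for 48 hours post-catheter insertion".

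**Safety Population.** SAP 3.2.2: "The Safety Population will include all participants in whom a block catheter was placed, and a dose of study treatment was administered". Patients are classified by treatment received. SAP 3.5 makes this the primary population for safety, and SAP 3.2 defines no wider safety set. On the events themselves, Protocol 6 says: "Adverse effects that will be specifically collected include infection, hematoma/hemorrhage, vascular injury, pneumothorax/hemothorax", followed by allergic reaction, nausea and vomiting, pruritus and local anaesthetic systemic toxicity (LAST).

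**The concern.** The two rules are separate, but both decide how well harms are seen.

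The first is a mismatch of time scales. Exposure lasts two days. Protocol 6 says that signs of LAST generally appear within minutes, with severe signs up to 6 hours after the first symptoms, and needle injuries arise at insertion. Most of what the DSMB needs is known by discharge. If the review waits for the 3-month telephone visit, recruitment continues in the meantime, and those extra patients are exposed before anyone has looked at the accumulated events by arm.

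The second is a mismatch between event and denominator. In Protocol 3.6 the needle enters the plane and the catheter is advanced first; study drug is connected and the first bolus given afterwards. Pneumothorax, vascular injury and haematoma can therefore occur before any dose, and such an injury is a plausible reason for never starting the infusion. That patient is then outside the set on which the safety tables are built. At stake is the absolute risk of inserting the catheters, which a clinician would want to know.

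**Working it through.** **Timing.** The plan gives no figure for how many patients will have been randomised at the review, so there is none to reproduce beyond the trigger itself: 0.50 × 340 = 170.

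Inputs from the documents: 340 patients (Synopsis; SAP 2.2.2); last visit at 3 months ± 4 weeks, outer limit 6 months (Protocol 5.1, 5.2); study duration 1-2 years (Synopsis).

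Assumptions: recruitment is even; the 1-2 years is all recruitment (no rate is stated); the trial population means the 340; hospital stay is about a week, or 0.25 month.

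Formula: randomised at review = min(340, 170 + monthly rate × months to the trigger). The rate is 340/24 = 14.17 or 340/12 = 28.33 per month.

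| Trigger | 24-month recruitment | 12-month recruitment |
|---|---|---|
| Discharge (0.25 month) | 170 + 3.5 = 173.5 (51%) | 170 + 7.1 = 177.1 (52%) |
| 3-month visit | 170 + 42.5 = 212.5 (62.5%) | 170 + 85 = 255 (75%) |
| About 4 months (late edge of window) | 170 + 56.7 = 226.7 (67%) | 170 + 113.3 = 283.3 (83%) |
| 6 months (outer limit) | 170 + 85 = 255 (75%) | 170 + 170 = 340 (100%) |

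On the scheduled visit, waiting instead of using discharge adds 2.75 months of recruitment: 2.75 × 14.17 = 39 to 2.75 × 28.33 = 78 further patients.

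Two variations raise the percentages:

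- If the 1-2 years includes 3 months of follow-up, recruitment lasts 9 to 21 months. The 3-month figures become 170 + 3 × 340/9 = 283 (83%) and 170 + 3 × 340/21 = 219 (64%).
- If 25% never complete follow-up and 170 completers are needed, 170/0.75 = 226.7 must first be randomised. The 3-month figures become 226.7 + 42.5 = 269 (79%) and 226.7 + 85 = 312 (92%). The 25% is borrowed from the sample-size attrition rate, which the plan does not tie to follow-up.

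**Counting.** Let *x* be insertion-related events among *n* patients in whom insertion was attempted, and *k* the events among the *m* of them who were never dosed. The plan would report (*x* − *k*)/(*n* − *m*). This lies below *x*/*n* exactly when *k*/*m* > *x*/*n*, that is, when injury is commoner among undosed patients than overall. If insertions fail for unrelated reasons, the count drops but the rate is not biased. If injury is itself a reason not to dose, the rate is biased downward.

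The documents give no rate of abandoned insertion. Assuming 1-5% of 340, *m* is 3.4 to 17. Protocol 6 cites about 1% pneumothorax for a different block. If injury and abandonment were unrelated, the expected number lost would be 0.01 × 3.4 = 0.03 to 0.01 × 17 = 0.17. The number is higher if injury causes abandonment, by an amount that the documents cannot supply.

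**The case against.** **The DSMB is not blind until then.** It can request further analyses, Protocol 6 builds safety monitoring into every visit, and Protocol 3.7 provides for code-breaking. A charter is named in the Summary of Changes but is not among these documents; it may set earlier reports. This stands: a reader might infer that harms go unnoticed for months, and the documents do not support that. What remains is that 6.1 schedules no earlier aggregate report.

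**Six months is only an outer limit.** This also stands. The 100% figure needs both 12-month recruitment and follow-up taking the full 6 months. Nor can it be said that the review protects few patients: at the 3-month visit, 340 − 255 = 85 to 340 − 212.5 = 127.5 patients (25% to 37.5%) are still to be randomised.

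**The Safety Population gap is narrow.** The first bolus follows placement directly, so an injury recognised after it is counted. Both arms receive catheters, so mainly the absolute risk is affected, not the comparison between arms. LAST requires a dose and cannot be lost this way. A dosed, as-treated safety set is common, and calling it primary does not bar other listings. All of this is fair, but no other set or listing is planned.

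**Two stronger readings fail.** A reader might infer that the excluded cases are the most serious ones; nothing in the documents shows this. A reader might also reason that, with about 3 pneumothoraces expected in 340 (0.01 × 340 = 3.4), one lost case cuts the rate by a third. The 1% comes from another block and another incision, and the one lost case is hypothetical.

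**An earlier trigger has a price.** Fewer post-discharge events, late infection among them, would be available at the review. That is a real but small cost.

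**Conclusion.** Both parts hold in limited form, and both are worth changing.

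The scheduled review is tied to a term that 6.1 leaves undefined. On its natural reading, the 3-month visit, about 63-75% of patients are already randomised by then, against just over 50% with a discharge trigger: some 39 to 78 patients more. This rests on even recruitment over 12 to 24 months and a hospital stay of about a week. It concerns the timing of the planned aggregate review only.

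The Safety Population omits insertion injuries recognised before any dose when the infusion is never started. The absolute insertion-complication rate is then biased downward to the extent that injury leads to non-dosing. The size is unknown and probably small. Drug-related harms are unaffected, and the comparison between arms should be little affected.

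**What to change.** (a) **Protocol 6.1 and the DSMB charter:** trigger the review when 170 patients have reached hospital discharge, using all in-hospital safety data plus whatever post-discharge data are available. At the least, define follow-up in 6.1. If the charter already schedules earlier reports, 6.1 should say so.

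(b) **SAP 3.2.2 and 3.5.1:** summarise insertion-related adverse events in all participants in whom catheter insertion was attempted, placing undosed patients in their assigned arm. Keep the dosed, as-treated set for drug-related events.

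The cost is about one sentence in each document and one extra table. For (a) the price is fewer post-discharge events at that review; the DSMB keeps its discretion to ask for more. For (b) the case report form must identify attempted insertions without a dose. If the half-way review has already been held, (a) no longer applies and (b) stands alone; SAP section 1 has the SAP finalised before database lock, so (b) should be settled by then.

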## **7. Statistical Analysis and Sample Size Calculation**

For the primary analysis, we will perform linear regression, adjusted for sex (clinical stratification factor) and intraoperative opioid MME to assess the comparison between trial groups, with a P-value threshold of 0.05 being considered significant. If residuals indicate substantial violations of the linear regression assumptions, alternate methods will be attempted, such as analyzing log-transformed data, using bootstrap hypothesis testing or two-sample t-tests without equal variance. A modified intention-to-treat analysis will be employed, including only patients in whom a block catheter was placed, and a dose of study drug was administered. The time-to-event outcomes will be modelled simultaneously using a multistate framework. This approach will handle competing risks, such as death, and treat other non-fatal events, that could be related to each other, as intercurrent events. Sensitivity analyses using complete intention-to-treat and per protocol populations will also be conducted. Categorical data will be summarized by frequencies and percentages, and continuous variables by means and standard deviations (plus medians and interquartile ranges for non-symmetric data).

In order to detect a mean difference of 10 MMEs, assuming a standard deviation of 25 and an alpha value of 0.05, a sample size of 133 participants per group would be required to provide a power of 90%. Assuming an attrition rate of 25%, approximately 340 patients will need to be randomized for the primary modified intention-to-treat analysis.

Pre-specified subgroup analyses of the primary outcome include:

- Age
- Race/Ethnicity
- Sex/Gender
- Diabetes status
- BMI
- Type of operation
- Site

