### *2.2.2 Sample Size Determination*

To detect a mean difference of 10 milligram morphine equivalents (MMEs), assuming a standard deviation of 25 and a 2-sided type 1 error rate of 5%, a sample size of 133 participants per group would be required to provide a power of 90%. Assuming an attrition rate of 25%, approximately 340 patients will need to be randomized.

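### At the stated 25% attrition, 340 randomised patients leave 255 evaluable, not the 266 needed, so the plan's sample size, attrition and 90% power do not agree

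*Combined protocol and SAP*

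**What the plan says.** Protocol section 7 gives the calculation in two sentences. The target and spread are "In order to detect a mean difference of 10 MMEs" and "assuming a standard deviation of 25 and an alpha value of 0.05". From these, "a sample size of 133 participants per group would be required to provide a power of 90" per cent. The attrition step follows: "Assuming an attrition rate of 25%, approximately 340 patients will need to be randomized". To its end, that sentence reads "approximately 340 patients will need to be randomized for the primary modified intention-to-treat analysis". The protocol therefore ties the 340 to the primary analysis population, not to completeness of the later telephone follow-up.

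SAP section 2.2.2 repeats the same figures and adds that the test is two-sided: "assuming a standard deviation of 25 and a 2-sided type 1 error rate of 5" per cent. Protocol section 3.1 sets the allocation: patients "will be randomized in a 1:1 fashion into the intervention or control group".

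The synopsis lists the sample size as 340 with no qualifier. Neither document shows how 25% attrition leads from 266 to 340.

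**The concern.** To be left with a required number of evaluable patients after a fraction *d* is lost, that number is divided by (1 − *d*). Applied to 266 with *d* = 0.25, this does not give 340. Attrition of 25%, a randomised total of 340 and power of 90% then form a set in which at most two can be true together.

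This passage justifies the enrolment target for the primary endpoint and is likely to be quoted in the trial report, where anyone can check it in one line. Losses would not be made good in the analysis either: SAP section 3.1.6 rules out imputing missing efficacy data, and the mITT population (SAP section 3.2.1) omits randomised patients who had no catheter placed or received no dose. At stake is the accuracy of the stated power.

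**Working it through.** **Inputs.** Difference 10 MME, SD 25, 133 per group, power 90%, attrition 25% and 340 randomised (protocol section 7 and SAP section 2.2.2); alpha 0.05, two-sided (SAP section 2.2.2); allocation 1:1 (protocol section 3.1).

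**Step 1: reproduce the evaluable number.** The standardised difference is 10/25 = 0.4.

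- Normal approximation: n per group = 2 × (1.960 + 1.282)² / 0.4² = 131.3, rounded up to 132.
- Two-sample t-test: n per group = 132.3, rounded up to 133. Power at 133 per group is 90.1%.

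The plan's 133 is therefore the unadjusted two-sample t-test result, and its evaluable target is 2 × 133 = 266.

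**Step 2: inflate for attrition.** Randomised N = evaluable N / (1 − attrition).

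- From 133 per group: 266 / 0.75 = 354.7, so 355, or 356 (178 per group) for equal arms.
- From 132 per group: 264 / 0.75 = 352.

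Neither gives 340. Against the stated inputs, 340 is 15 to 16 patients short (15/355 = 4.2%; 16/356 = 4.5%). Multiplying by 1.25 in place of dividing by 0.75 is a common slip. It gives 266 × 1.25 = 332.5, which is not 340 either, although it would become 340 if rounded up to the next ten.

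**Step 3: work forward from 340.**

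| Quantity | Calculation | Result |
|---|---|---|
| Evaluable patients at 25% attrition | 340 × 0.75 | 255 (127 to 128 per arm) |
| Shortfall against target | 266 − 255 | 11 |
| Power at 127.5 per arm, t-test | standardised difference 0.4, two-sided 5% | 88.9% |
| Power at 127.5 per arm, normal approximation | same inputs | 89.1% |
| Attrition at which 133 per group is just kept | 1 − 266/340 | 21.8% |
| Attrition at which t-test power is exactly 90% | 1 − (2 × 132.31)/340 | 22.2% |

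The last two rows differ only because 133 is 132.3 rounded up.

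**The case against.** The strongest reply accepts the arithmetic and disputes its importance.

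- **The loss is tiny.** Power falls from 90.1% to 88.9%, or 1.2 points. With 255 evaluable patients, 90% power still holds for a difference of 10.19 MME instead of 10, or for an SD of 24.54 instead of 25. Both inputs are round planning values and are less certain than that. This stands, and it sets the weight of the point.
- **Covariate adjustment may recover it.** The primary analysis adjusts for sex and intraoperative MME, and SAP section 3.4.1 adds BMI. If 25 is the unadjusted SD, covariates explaining about 3.7% of the outcome variance would restore 90% power with 255 patients; 5% would give 90.4% and 10% would give 91.8%. This is plausible, but neither document states an explained variance or takes credit for adjustment, and the 133 is the unadjusted figure. It means that 88.9% describes the plan's own calculation and is not a forecast of the power of the adjusted analysis.
- **The total is only approximate.** Both documents qualify 340 in this way. The gap is still more than 4%, and a required minimum is rounded up, not down.
- **340 may simply be 332.5 rounded up.** This is possible, but it is an inference that the documents do not support or exclude. It would explain the mismatch without removing it.
- **Actual attrition may be below 25%.** If so, 25% is the figure to correct. The inconsistency remains until one of the three is changed.

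**Conclusion.** The point holds. Protocol section 7 and SAP section 2.2.2 both state three figures that cannot all be true, and nothing else in the documents reconciles them. Under the stated inputs, 340 randomised with 25% attrition gives 255 evaluable patients and 88.9% power; 90% power at that attrition needs 355 to 356 randomised.

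The practical consequence is small, about one percentage point of power. It is an inconsistency in the justification and does not show a materially underpowered trial. The result assumes an unadjusted two-sample t-test with equal arms and a common SD of 25, and that the 25% is lost from the primary mITT analysis, as protocol section 7 implies. It does not depend on how 340 was reached.

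**What to change.** Keep 340 and make the power statement match it. In protocol section 7 and SAP section 2.2.2, replace the attrition sentence with text such as: *With 340 patients randomised and 25% attrition, 255 evaluable patients give about 89% power for a difference of 10 MME (SD 25, two-sided alpha 5%); 133 per group, and so at least 90% power, is retained if attrition is no more than 21.8%.*

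If the sponsor has grounds to expect lower attrition, or would rather randomise 355 to 356, either also resolves the conflict, provided the same choice appears in both documents and in the synopsis where it is affected.

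The cost is one sentence in each document and a slightly less favourable stated power. The protocol edit may need to go through the ethics board's amendment process, as previous protocol changes did. If the documents can no longer be amended, the same sentence can go in the trial report.

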## **8. Data Collection and Storage**

### *Trial Management*

The Applied Health Research Centre (AHRC) of St. Michael's Hospital will be coordinating centre for the study. The AHRC will provide project and data management, as well as trial monitoring. The AHRC is a comprehensive clinical trials unit and is the official clinical trials unit for the University of Toronto. REDCap will be utilized for randomization and eCRF data entry. REDCap is a web-based electronic data capture system with built-in quality checks to ensure data accuracy and integrity.

